## Study plan

### Study design

This is an open-label, randomized, comparative, double-arm, multicenter, phase III study to assess DFS, OS, and safety profiles with tegafur-uracil following an adjuvant oxaliplatin-based regimen as maintenance therapy for 1 year in patients with stage III colon cancer after radical resection in Taiwan (see Additional file 1 for the SPIRIT 2013 checklist).

### Patient number

Eligible patients will be randomized in two arms in a 2:1 ratio to reach an approximate total of 546 patients.

### Study schedule

Study date: the time of obtaining an approval letter from both regulatory authority and Institutional Review Board (IRB).Expected recruitment rate: 24 patients/monthRecruitment date: at least 2 yearsStudy duration: at least 5 years

### Visit schedule

The schedule of assessments (see ‘Assessment schedule’ below for details) indicates the number and timing of the planned visits, which must be followed as accurately as possible. Moreover, the visit schedule must be accurately followed.

### Treatment duration

Treatment will be administered for up to a maximum of 1 year, and in case of disease progression, intolerable toxicity, or consent withdrawal during the study, the patients will be withdrawn.

## Trial treatment

### Data on investigational product (Table 1)

**Table 1 Tab1:** Data on the investigational product

Name of active ingredients	Tegafur	Uracil
Description	Tegafur occurs as a white crystalline powder. It is soluble in methanol, sparingly in water and ethanol, and slightly in ether. It is soluble in dilute sodium hydroxide.	Uracil occurs as a white crystal or crystalline powder, free of odor or taste. It is slightly soluble in water; slightly soluble in methanol, ethanol and acetone; and insoluble in ethyl acetate and chloroform.
Structure		
Chemical name	1-(2-tetrahydrofuryl)-5-fluorouracid 5-fluoro-1-(2-tetrahydrofuryl)-2,4 (1H,3H)-pyrimidinedione (IUPAC)	2,4(1H,3H)-pyrimidinedione
Molecular formula	C_8_H_9_FN_2_O_3_	C_4_H_4_N_2_O_2_
Molecular weight	200.17	112.09
Melting point	166 °C–171 °C	Approximately 335 °C
Contents	Each capsule contains 100 mg tegafur and 224 mg uracil.	
Storage condition	Below 30 °C	

#### Preparation and administration of the investigational product

Tegafur-uracil capsules (200 mg) will be administered twice daily (400 mg daily) at regular intervals. They will be administered whole and either 1 h before or after food consumption in the morning and evening.

### Labeling and supply

Tegafur-uracil is commercially available and supplied by the investigator’s pharmacy. The batch numbers of the used drugs will be diligently obtained and recorded.

### Storage

The drugs will be stored at below 30 °C. Procedures for the appropriate handling and disposal of anticancer medications will be followed.

### Dosage and treatment regimens

Eligible patients will receive orally administered tegafur-uracil (400 mg daily; 100 mg/capsule, two capsules each time, twice daily) and folinic acid (30 mg daily; 15 mg/tablet, one tablet each time, twice daily) for 1 year.

### Dose modification

The dose after the first treatment will be modified on the basis of the highest toxicity degree graded according to National Cancer Institute Common Terminology Criteria for Adverse Events (NCI-CTCAE) v4.03For toxicities that are considered by the investigator to be unlikely to become severe or life-threatening and that do not result in a delay or interruption of therapy (e.g., alopecia and altered taste), treatment will be continued at the same dosing without reduction or interruption. No dose reductions or interruptions are required for anemia because it can be satisfactorily controlled by transfusionsFor the patients experiencing treatment interruption because of AEs for more than 2 weeks, treatment discontinuation will be considered (Table 2)

**Table 2 Tab2:** Dose modification

Toxicity (grade)	Dose modification
ANC <1000/mm^3^	Discontinue the treatment until ANC ≥1500/mm^3^; resume the treatment with the same dose
Platelets <50,000/mm^3^	Discontinue the treatment until platelets ≥100,000/mm^3^; resume the treatment with the same dose
Other toxicities	No dose modification or interruption required
Grades 1 and 2	Discontinue the treatment until returns to baseline; resume the treatment to 200 mg daily
Grades 3 and 4	
*ANC* absolute neutrophil countDiscontinuation of study participation

If the patients experience any of the following consequence during the study, they will be withdrawn from the study treatment:Disease recurrenceIntolerable toxicityConsent withdrawalInvestigator discretion

All information regarding the withdrawal will be recorded in the Case Report Form (CRF)

### Prestudy, concomitant, and post-study treatments

Concomitant treatmentThe use of all concomitant medications and supportive therapies at baseline will be recorded throughout the study.Prohibited treatmentTreatment for cancerExcept for the assigned study treatment, no other treatments known to exert an anticancer effect can be used during the trial (e.g., other chemotherapies, hormonal therapy, immunotherapy, antibody therapy, radiotherapy, thermotherapy, surgery, and IPs)FlucytosineRadiotherapy for supportive careOther IPs
Treatment with precautionCoumarin anticoagulantsThe patients treated with coumadin anticoagulants, such as warfarin, and concomitantly with tegafur-uracil will be regularly monitored for alterations in prothrombin time or the international normalized ratioPhenytoinThe patients taking phenytoin concomitantly with tegafur-uracil will be regularly monitored for an increased phenytoin plasma concentration

## Study measurement and endpoints

### Screening and demographic measurements

The assessment schedule is illustrated in the ‘Assessment schedule’ section below. Each patient must sign and date an informed consent form before undergoing any study specific procedure, unless the procedure is considered the standard of care.

Screening procedures will be performed before the first treatment according to the assessment schedule within the required timeline.Demographic and past medical historyA complete medical history will be obtained at the screening visit. The medical history will include demographic information as well as any information pertinent to a CRC diagnosisPhysical examination, vital signs, and performance statusPhysical examination will be conducted, and vital signs and the performance status will be reported within 14 days before the first treatment and be repeated at every visit until study completion.The vital signs, including height, weight, blood pressure, and performance status, will be recorded according to the ECOG ScaleHematological and biochemical testsHematological and biochemical tests will be performed within 14 days before the first treatment. If any required hematological or biochemical values do not meet the eligibility criteria, the tests will be repeated before enrollment. If the tests performed within 7 days before the first treatment fulfill the eligibility criteria, tests are not required on day 1 of treatment.The hematological test comprises complete blood count (CBC) and differentiation count (D/C). CBC includes hemoglobin, hematocrit, erythrocytes, leukocytes, neutrophils, and platelets; The D/C will be calculated to obtain the ANC.The biochemical test measures albumin, alkaline phosphatase, ALT, AST, bilirubin (total and direct), blood urea nitrogen (BUN), and creatinineCarcinoembryonic antigenCarcinoembryonic antigen (CEA) will be assessed every 3 months before the first treatment and will be repeated every 3 months in the first and second years and every 6 months thereafterComputed tomography or magnetic resonance imagingComputed tomography (CT) or magnetic resonance imaging (MRI) will be annually performed in the first 2 years or if disease recurrence is suspected. The acceptable window for scheduling the imaging studies is ±1 week. Subsequently, CT or MRI will be performed only on suspected disease recurrence thereafterAbdominal echoAbdominal echo will be performed every 6 months. However, its actual implementation will be based on clinical practice. The schedule of CT or MRI and abdominal echo are crossed over, and the typical interval is 6 months. CT or MRI is the main examination when the schedule is duplicatedChest X-rayChest X-ray will be annually performedAdverse eventsAEs will be recorded from the first treatment to treatment completion

### Efficacy measurements and endpoints

In this study, we set 3-year DFS and 5-year OS as the primary endpoints and the differences the difference in survival distributions between two groups were analyzed using the log-rank test.Three-year disease-free survival (DFS)CEA and CT or MRI scan will be performed within 28 days before the treatment. The CEA level will be the efficacy measurement for endpoints and will be performed within every 3 months before the first treatment and repeated every 3 months in the first and second year and every 6 months thereafter. CT or MRI can be performed annually in the first 2 years or on suspected disease recurrence. The acceptable window for scheduling the imaging studies is ±1 week. Thereafter, CT or MRI will be performed only on suspected disease recurrence. DFS will be measured from start from the date of randomization to the date of disease recurrenceFive-year overall survival (OS)OS will be measured from the start from the date of randomization to the date of deathSafety profileHematological and biochemical tests should be closely monitored during the treatment period because bone marrow depression, liver dysfunction, dehydration, anorexia, nausea, vomiting, and other AEs that have been reported in clinical treatment. The evaluation results would be included in the date or symptoms mentioned in the package insert

### Safety measurements and endpoints

Hematology and biochemistryHematological and biochemical assessments will be performed within 7 days before enrollment and at each clinical visit, as reported in Table 3. The clinically relevant findings will be recorded and graded according to NCI-CTCAE v4.03

**Table 3 Tab3:** Flowchart for pretreatment and post-treatment investigations

Study period	Screening	Study treatment	Treatment completion	Post treatment	
Day/month/year	−28 to 0 days	Clinical visit	Any time	2nd year	3rd–5th years
Informed consent	X				
Medical history	X				
Demography	X				
Pregnancy test, if appropriate	X				
Physical examination, ECOG, vital signs	X	X^a^	X		
Hematology	X	X^a^	X		
Biochemistry	X	X^a^	X		
CT or MRI^b^	X		X	X	
Abdominal echo^c^		X^c^		Every 6 months	Every 6 months
Carcinoembryonic antigen (CEA)	X	X^a^	X	Every 3 months	Every 6 months
Study treatment^d^		X			
Adverse events		X	X^e^		

^a^It will be repeated once every 3 months, including the assessment of physical status, Eastern Cooperative Oncology Group (ECOG) status, vital signs, hematological and biochemical data, and CEA, during the study treatment

^b^Computed tomography (CT) or magnetic resonance imaging (MRI) will be repeated every 12 months for the first 2 years or on suspecting disease recurrence. Thereafter, CT or MRI will be performed only on suspected disease recurrence

^c^Abdominal echo will be repeated every 6 months. However, actual implementation will be based on clinical practice. The schedule of CT or MRI and abdominal echo are crossed over; the examinations are typically performed at an interval of 6 months. CT or MRI is the main examination used when the schedule is duplicated

^d^Treatment in arm A will be started within 7 days after the randomization

^e^The patients will be followed for the occurrence of serious adverse events (SAEs) until 30 days after the last dose of study medication or introduction of an additional antitumor therapy, whichever occurs firstOther toxicitiesAny toxicities other than those observed in hematological and biochemical assessments will be recorded and graded according to NCI-CTCAE v4.03

## Assessment schedule (Table 3)

### Data management and statistical methods

#### Data management

CRFs will be provided for recording the data. Data will be recorded directly and legibly onto the CRFs by using a black-ink pen. If any data are unavailable, reason for omissions will be mentioned on the CRFs. Corrections will be made legibly and initiated and dated by an approved personnel; the reasons for marked changes will be provided. Correction fluid or covering labels will not be used.

#### Statistical methods and sample size determination

This is an open-label, randomized, comparative, double-arm, multicenter, phase III study of tegafur-uracil following an adjuvant oxaliplatin-based regimen in patients with stage III colon cancer after radical resection.Statistical evaluationStatistical analysis methodsA comprehensive statistical analysis plan will be prepared before database lock. The patients will be categorized into the Full Analysis Set (FAS), per protocol (PP), and safety populations according to the following definitions:Full Analysis Set (FAS):The FAS is defined as containing all registered and randomized patients who received at least one dose of the study treatment without major protocol violations, such as noncompliance with the eligibility criteria, or other major violations (defined before database lock) during the studyIntent-to-treat (ITT):The ITT population is the subset of the FAS population, and as all randomized patients irrespective of treatment receivedPer protocol (PP):The PP population is the subset of the ITT population and subjects who complete 12 months of tegafur-uracil treatment/observation with at least one biomarker assessment post treatment. The subject with confirmed early disease recurrence/relapse would be included in the PP population. The patients with confirmed early disease recurrence and relapse will be included in the PP population.All the efficacy endpoints will be analyzed in the FAS and PP populations. The main assessment will be performed on the basis of the PP population.The safety population is defined as all patients who are exposed to at least one dose of the study treatment and who are available for obtaining follow-up safety information
Statistical analysesDemographic and baseline measuresAll demographic and baseline data will be summarized and listed in detail. For continuous variables, the descriptive statistics, including the patient number, mean, median, standard deviation, and range (minimum-maximum) will be presented; frequency tables will be displayed for categorical data. If demographic and baseline measures are significant, their inclusion in the analysis model will be consideredThree-year disease-free survival (DFS)Three-year DFS will be defined as the percentage of patients alive without disease recurrence at 3 years measured from the randomization date. The 3-year DFS will be evaluated using the Kaplan-Meier method, and the analysis will be presented in descriptive statistics, presented by a point estimate and 95% confidence interval. The results will be summarized in the form of the sample size, mean, standard error, median, percentiles, and range by descriptive statistical methodsFive-year overall survival (OS)Five-year OS will be defined as the percentage of patients alive at 5 years measured from the randomization date. The 5-year OS will be evaluated using the Kaplan-Meier method, and the analysis will be presented in descriptive statistics, presented by a point estimate and 95% confidence interval. The results will be summarized in the form of the sample size, mean, standard error, median, percentiles, and range by using descriptive statistical methodsSafety profileAEs will be summarized using NCI-CTCAE v4.03 and the preferred term. The incidence and percentage of patients with at least one occurrence of a preferred term will be included according to the most severe NCI-CTCAE v4.03 grade. Laboratorial toxicity will be presented according to the highest NCI-CTCAE v4.03 grade by cycle

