**Fig. 2 Fig2:**
[figure not shown]
Flowsheet for pre/post-treatment investigations

Patient eligibility criteria will be established before treatment enrollment.

Following the completion of an adjuvant oxaliplatin-based regimen within 3 weeks with no evident disease recurrence, all eligible patients will be randomly assigned to either arm A (maintenance therapy) or arm B (observation arm) in a 2:1 ratio (364 and 182 patients in the tegafur-uracil and observation groups, respectively). Treatment in arm A will be started within 7 days of the randomization.

If the patients report disease recurrence, intolerable toxicity, or consent withdrawal or are removed according to the investigator’s discretion during the study period, they will be withdrawn from the study. If a patient wishes to discontinue the study, the corresponding data will not be reused, and the patient will not be allowed to re-enter the study.

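### The FAS demands a dose that observation patients never receive, ITT is placed inside that smaller set, and no efficacy analysis is assigned to all randomized patients

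*Protocol article*

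**What the plan says.** All the definitions stand in the protocol article under Statistical methods and sample size determination.

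- **FAS:** "all registered and randomized patients who received at least one dose of the study treatment without major protocol violations". Major violations include failing the eligibility criteria and other on-study violations, with the list to be settled before database lock.
- **ITT:** one sentence calls it part of the FAS and also defines it as everyone randomized, whatever they received.
- **PP:** "The PP population is the subset of the ITT population and subjects who complete 12 months of tegafur-uracil treatment/observation", with at least one post-treatment biomarker assessment. Patients with confirmed early recurrence are also kept.
- **Use:** "All the efficacy endpoints will be analyzed in the FAS and PP populations", and then "The main assessment will be performed on the basis of the PP population". ITT is given no analysis.

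Under Trial enrollment method, patients are "randomly assigned to either arm A (maintenance therapy) or arm B (observation arm) in a 2:1 ratio", with "364 and 182 patients in the tegafur-uracil and observation groups, respectively". In Table 3 the footnote to the study-treatment row mentions one arm only: "Treatment in arm A will be started within 7 days after the randomization". Dosage and treatment regimens describes tegafur-uracil with folinic acid and nothing for arm B.

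**The concern.** A full analysis set is meant to preserve the randomized comparison. Here its entry condition is an event that can happen in only one arm. A programmer applying the rule as written would build an FAS with no controls. One applying it to arm A alone would drop patients who never start drug from that arm and keep every control. Either way membership depends on something that follows allocation and differs by arm.

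The violation exclusion adds to this. Removing patients for on-study violations makes the FAS resemble a second per-protocol set, in an open-label trial where the list need only be settled before database lock. The sentence that would have protected the randomization, the ITT definition, contradicts itself and is tied to no analysis.

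At stake is who enters the comparison in a phase III superiority trial. Two statisticians working from this text could build different datasets and both claim to follow the protocol.

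**Working it through.** The check is one of set membership. Sample size and power play no part in it.

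**Inputs** (protocol article): 364 patients in arm A and 182 in arm B, 364 + 182 = 546, a 2:1 split (364/182 = 2). Study drug is described for arm A only. The definitions are those quoted above.

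**Step 1. FAS.** Membership needs randomization, at least one dose, and no major violation.
- Arm A: at most 364.
- Arm B: no dose is given, so 0 of 182.
- Read literally, 182/546 = 33.3% of randomized patients are outside the FAS before any violation is considered, and the FAS has no control arm. No other wording in the FAS definition readmits arm B.

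**Step 2. ITT.** The two halves of the sentence give different sets.
- As part of the FAS: at most 364 patients, none from arm B.
- As everyone randomized: 546 patients, 182 from arm B.
- A set of 546 cannot lie inside a set of at most 364. Even if arm B were exempt from the dose rule, a single never-starter or major violator would make the two halves disagree. The nesting is inverted: the FAS should lie within the randomized set, not the reverse.

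**Step 3. PP.** It inherits whichever ITT is meant.
- Through the chain PP within ITT within FAS, arm B would be empty.
- But the PP wording names completers of observation, who exist only in arm B.
- So the text is contradictory on ITT and PP; it does not consistently exclude controls.

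**Step 4. Dose rule applied to arm A only.** Patients lost from arm A = 364 × (share never starting); patients lost from arm B = 0. The article gives no such share. As a scale and not a forecast: 1% gives 364 × 0.01 = 3.64, and an assumed 5% gives 364 × 0.05 = 18.2. All come from one arm.

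**Step 5. Which analysis covers all 546?** Efficacy is assigned to the FAS (dosed and violation-free) and to PP (12-month completers plus confirmed early recurrences), with PP as the main set. ITT has no assignment. So none does.

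**Related wording.** The safety population also requires at least one dose, although Secondary objectives promises a safety comparison of both arms. This suggests that the dose condition was written without the untreated arm in mind.

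**The case against.** The strongest reply is that nobody intends a trial without controls. That stands. The PP definition expressly admits observation completers, and half of the ITT sentence takes in everyone randomized. A reader might infer from the nesting that no efficacy set contains any arm B patient, or that 0 of 182 applies to FAS, ITT and PP alike. The document does not support that. For ITT and PP the conclusion comes only from preferring the subset wording over the explicit membership wording, and ITT is not an efficacy set here at all. The figure of 0 of 182 stands for the FAS alone.

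A reader might also infer that violators will be removed after outcomes by arm have been seen. The text does not show this. It requires the list before database lock, gives ineligibility as the example, and does not say who settles the list or what they will know. In an open-label trial it is a risk and no more. Excluding ineligible patients alone might be defended; excluding patients for violations during the study is harder to defend in a set called full analysis.

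Third, the number of never-starters may be small, since arm A is to begin within 7 days of randomization. That is fair: the direction is known and the size is not.

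Finally, rewording the FAS alone would leave the main result untouched, because the main assessment is on PP. This also stands, and the fix has to go further for that reason.

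The unseen statistical analysis plan does not answer the point. These are stated definitions that conflict, not details left for later. A plan that followed them would inherit the conflict, and one that departed from them would disagree with the protocol.

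**Conclusion.** The concern holds in this form. The FAS definition cannot be met by an observation arm: 0 of 182 controls qualify as written. The ITT definition is impossible as stated. Whether controls belong to ITT and PP is contradictory, with the evident intent that they do. On the lenient reading the FAS still loses never-starters from arm A only, about 3.6 patients per 1% of 364, and loses on-study violators as well. No efficacy analysis is assigned to all 546 randomized patients.

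This rests on reading study treatment as the tegafur-uracil regimen, which the article describes for arm A only, and on no dose being given in arm B. The rates of never starting and of major violation are not stated, so the resulting bias cannot be sized. The definitions must be corrected before they are used to build the analysis sets.

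**What to change.** 1. Define FAS and ITT as one set: all randomized patients, analysed in the arm assigned, with no condition on dose received or protocol violations.
2. Delete the clause that places ITT inside the FAS.
3. Define PP as a subset of that set, keeping its reference to both treatment and observation.
4. Name the all-randomized set for the main efficacy analysis, with PP as supportive. Without this step the correction does not reach the main result.
5. Reconcile the withdrawal wording. The abstract and Trial enrollment method withdraw patients from the study for recurrence, toxicity, consent withdrawal or investigator decision, whereas Dose modification speaks of leaving study treatment. The first two also say that data of those who discontinue are not reused. The text should make clear that recurrence and survival outcomes of patients who stop treatment still count in the analysis, within the consent they have given.

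**Cost:** reworded definitions and no additional patients. Step 5 is more than editorial if current practice ends follow-up when treatment stops, because outcomes would then have to be collected after that point.

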### Reporting

Adverse event reportingAll AEs will be reported from the time that a signed and dated Informed Consent Form is obtained until the completion of the last study-related procedure.All AEs, regardless of their seriousness, severity, or presumed relationship to the study therapy, will be recorded using medical terminology in the source document and CRF. Whenever possible, diagnoses will be performed if signs and symptoms are caused by a common etiology. Investigators will record in the CRF their opinions concerning the relationship of the AE to the study therapy. All measures required for AE management will be recorded in the source documentSeverity and causalityAE severity and relationship to the study medication will be evaluated and recorded in the CRFSeverity categories (Table 4)

**Table 4 Tab4:** Severity categories of adverse events (AEs)

Severity	Description
Mild	NCI-CTCAE v4.03 grade 1
	The AE does not limit daily activities; the patients may experience slight discomfort
Moderate	NCI-CTCAE v4.03 grade 2
	The AE results in some limitation of daily activities; the patients may experience considerable discomfort
Severe	NCI-CTCAE v4.03 grade 3
	The AE results in an inability to perform daily activities; the patients may experience intolerable discomfort
Life-threatening/disabling	NCI-CTCAE v4.03 grade 4
	The AE results in a disabling situation
	The AE results in a life-threatening situation
Death	NCI-CTCAE v4.03 grade 5

*The term life-threatening in the definition of severe refers to an event, in which the patients are at a risk of death at the time of the event; it does not refer to an event which, hypothetically, might have caused death if it were more severe (ICH-E2A)Causality to study medication The causal relationship with the study medication will be judged considering a patient’s systemic conditions, complications, concomitant medications, combination therapies, and temporal relationship. A reasonable possibility of the relationship between an AE and the study medication will be categorized into two categories: yes (presence of a reasonable causal relationship) or no (absence of a reasonable causal relationship; refer to the Council for International Organizations of Medical Sciences for definition of causality VI. If the investigator judges the relationship to be a “yes,” the event will be considered an adverse drug reaction (Table 5).

**Table 5 Tab5:** Adverse drug reaction (ADR)

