### Follow-up

For safe follow-up, each patient will be followed for the occurrence of SAEs until 30 days after the last dose of the study medication or introduction of an additional antitumor therapy, whichever occurs firstAll SAEs that have not been resolved by the end of the study or upon discontinuation of the patient’s participation in the study will be followed until any of the following occurs:The event is resolvedThe event is stabilizedThe event severity returns to baseline, if a baseline value is availableThe event can be attributed to agents other than the study medication or to factors unrelated to the study proceduresWhen obtaining additional information is unlikely (the patients or health care practitioners refuse to provide additional information or the patients are lost to follow-up despite diligent follow-up efforts)

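### The safety population requires a dose, so it leaves out the observation arm, and the adverse-event windows disagree on whether that arm is covered at all

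*Protocol article*

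**What the plan says.** Under Secondary objectives, the protocol plans to assess safety and compare it between the two arms. Under Trial enrollment method, patients are randomised to "arm A (maintenance therapy) or arm B (observation arm) in a 2:1 ratio (364 and 182 patients in the tegafur-uracil and observation groups, respectively"). Only one arm has a treatment start: "Treatment in arm A will be started within 7 days of the randomization".

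Under Statistical methods and sample size determination, the analysis set for safety is given as: "The safety population is defined as all patients who are exposed to at least one dose of the study treatment". A second condition is that follow-up safety information can be obtained.

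Collection of adverse events is described in four places:

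- **Screening and demographic measurements:** AE recording begins with the first treatment and ends when treatment is completed.
- **Safety measurements and endpoints, Table 3:** the AE row is marked only under study treatment and treatment completion. Footnote e follows SAEs "until 30 days after the last dose of study medication or introduction of an additional antitumor therapy", whichever comes first.
- **Follow-up:** the SAE rule is repeated: "each patient will be followed for the occurrence of SAEs until 30 days after the last dose of the study medication", or until a further antitumour therapy begins.
- **Reporting:** all AEs are reported "from the time that a signed and dated Informed Consent Form is obtained until the completion of the last study-related procedure".

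**The concern.** A comparison of safety between arms needs both arms in the analysis set and the same collection period in each. The protocol fixes a set that one arm cannot enter. It then gives several collection windows, most of which use a dose or the end of treatment as an anchor.

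A concurrent control matters here. Patients enter within 3 weeks of an oxaliplatin-based regimen (Inclusion criteria), and the Trial rationale links chronic sensory neurotoxicity to the cumulative oxaliplatin dose. Carry-over events are therefore plausible in both arms. In an open-label trial the observation arm is the direct way to see how much of the event rate in arm A would have occurred anyway. If a site records AEs only while a patient is on study treatment, the matching events in arm B are never written down, and no later analysis can restore them.

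**Working it through.** The plan states no figure for the safety set, so there is none to reproduce. The check applies the definition to the planned arms and then sets the windows side by side.

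**1. Who is in the safety set**

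Inputs: arm A 364, arm B 182, total 546 (Trial enrollment method); entry condition of at least one dose (Statistical methods and sample size determination).

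- Arm A: at most 364. The number falls with patients never dosed or without safety follow-up.
- Arm B: no dose is planned, so 0 of 182.
- Share of randomised patients left out: 182 / 546 = 33.3%.
- With observation patients admitted, the set holds up to 364 + 182 = 546.

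Reading observation as a form of study treatment does not help easily, because observation has no dose. The same section names observation when it means to include it: the per-protocol set covers "subjects who complete 12 months of tegafur-uracil treatment/observation with at least one biomarker assessment post treatment". The safety definition has no such words.

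**2. Which windows can be applied to arm B**

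| Place in the protocol | Start | End | Usable in arm B? |
|---|---|---|---|
| Screening and demographic measurements | First treatment | End of treatment | No: neither anchor exists |
| Table 3, AE row | Study treatment column | Treatment completion column | Unclear: the columns are named for treatment |
| Table 3 footnote e; Follow-up (SAEs) | Not stated | 30 days after last dose, or new antitumour therapy if earlier | The last-dose anchor does not exist; the other exists only if such therapy is started |
| Reporting | Signed consent | Last study-related procedure | Yes, in every patient |

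The first and last rows cannot both be followed: they differ at the start and at the end. The SAE rule could sit beside the first row as an extension for serious events, but it also stops earlier than Reporting whenever study procedures continue beyond 30 days after the last dose. Table 3 plans CEA and abdominal echo up to year 5.

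**3. What the comparison could offer once arm B is in the set**

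The protocol gives no expected event rates. Assuming the same incidence p in both arms, the half-width of a 95% interval for the difference is 1.96 × √[p(1 − p)(1/364 + 1/182)]:

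- p = 5%: 3.9 percentage points
- p = 10%: 5.3 percentage points
- p = 20%: 7.1 percentage points

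Under the literal definition no such interval can be formed in the safety set.

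**The case against.** The best defence is that this is loose wording, not an intended exclusion. The Full Analysis Set carries the same dose condition, the ITT set is said to lie within it, and the per-protocol set, which includes observation patients, lies within the ITT set. That nesting works only if the dose phrase was not meant to remove arm B. The protocol also promises a statistical analysis plan before database lock, where the set could be corrected. This is a fair account of the likely intent. It does not change what the definition says, and an analysis plan can redefine a population but cannot recover events that sites did not record.

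A reader might go further and infer that observation patients contribute no safety data, so that the comparison is impossible in any form. The protocol does not support that:

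- Reporting requires all AEs from consent onwards, with no exposure condition.
- Safety measurements and endpoints asks for haematology and biochemistry at each clinical visit, with relevant findings graded.
- Table 3 is a single schedule for both arms; only footnote d singles out arm A.

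A reader might also infer that all residual oxaliplatin toxicity would be charged to tegafur-uracil. That too goes beyond the text. An AE must be new or worse than baseline (Definitions), the investigator judges causality for each event (Reporting), and patients with haemoglobin below 9 g/dL, ANC below 1500/mm³ or platelets below 100,000/mm³ are excluded at entry. These safeguards limit misattribution, but they do not replace a control rate.

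**Conclusion.** The point holds as a fault of definition plus a conflict between collection rules. Read literally, the safety population excludes all 182 observation patients, 33% of those randomised, and the secondary safety comparison cannot be made in that set. Separately, the windows tied to treatment and the window tied to consent contradict each other, so collection of AEs in arm B depends on the section a site follows.

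The figure of 0 of 182 is membership of an analysis set, not a count of lost data. Where sites follow Reporting, arm B events exist and the comparison becomes possible once the set is redefined. Where they follow the screening section or a treatment-bound reading of Table 3, the events are lost. The protocol does not show how sites would divide between these, so the size of that loss cannot be stated. The conclusion rests on two assumptions: arm B receives no study drug, as the design describes, and no document outside this article already overrides the definition.

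**What to change.** 1. **Safety population.** Define it as arm A patients who took at least one dose, plus all randomised observation patients with safety follow-up, grouped by the treatment actually received.
2. **One window.** Reconcile Screening and demographic measurements, Table 3 with footnote e, Reporting, and Follow-up into a single AE/SAE collection window. Its start and end anchors should be the same in both arms and should not depend on drug exposure. A window counted from randomisation would serve, as would the one already in Reporting; the choice is the sponsor's.
3. **Visits.** State that the 3-monthly visits of Table 3 apply to arm B. Footnote a now ties them to the period of study treatment.

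The cost is small for arm B: AE recording in 182 patients, and confirmation that their visits take place. One consequence should be settled when the window is chosen. Trial enrollment method withdraws patients with recurrence or intolerable toxicity from the study, so a window of fixed length would need the protocol to say how safety data are collected after withdrawal. For those patients the change is more than wording. The correction should reach sites while AEs are still being recorded.
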